### Trial design {8}

The study design will be an exploratory, parallel-group, three-arm, cluster randomized controlled trial. Children aged ≥ 6 months to ≤ 59 months will be enrolled in 3 separate cohorts (16 clusters per cohort) to establish the effectiveness of different distribution channels; one cohort to estimate the direct effect of the SR using a reference channel (study personnel distribution); one cohort to estimate the protection to persons using a voucher to receive the SR; and one cohort to estimate the effect of the SR distributed by VHTs. Cohorts will be followed and RDT will be conducted at least once every 4 weeks to test for malaria or whenever a participant reports a recent history of fever.

## Methods: participants, interventions, and outcomes

### Study setting {9}

Bidibidi Refugee Settlement located in Yumbe District, Northern Uganda, is currently the second largest refugee settlement in the world. About 6% of the population in Bidibidi is living in grass thatched or Aluzinc roof houses with over 20% living in tarpaulin structures, with the majority of those being women and children under 18. Residents access medical care (health facilities, clinics, hospitals, Community Health Worker programs) by walking or cycling. Most health facilities are nearby and at most within 5 km of their home. Refugees have settled in the Bidibidi Refugee Settlement according to 5 Zones, with first arrivals going to Zone 1, then to Zone 2, similarly to other Zones. All factors pertaining to population movement have been taken into account in the loss to follow-up rate.

There is stable, perennial malaria transmission in 95% of the country, with *Anopheles gambiae *s.l. and *An. funestus *s.l., the most common malaria vectors. *Plasmodium falciparum* accounts for 98% of infections; both *P. vivax* and *P. ovale* are rare and do not exceed 2% of malaria cases in the country [11]. Uganda’s climate is largely tropical with two rainy seasons per year, March to June and October to November. The northern region, which forms one quarter of the country lies outside the tropical belt, and hence experiences only one rainy season, March to October [11].

This research study will be focused in Bidibidi Refugee Settlement Zones 1 to 4, as the study population is more stable than in other Zones. The 48 clusters to be delineated for subject enrolment and follow-up will include 70% refugee settlements and 30% adjoining host-community villages.

### Eligibility criteria {10}

All children aged ≥ 6 months to ≤ 59 months who report sleeping in selected study clusters > 90% of the nights of each month will be eligible for inclusion in the study. Children < 6 months to > 59 months with Hb ≤ 7 g/dL with no other serious illness will also be excluded from the study.

Persons who are participating in another clinical trial investigating a drug, vaccine, medical device, or procedure will also be excluded from the study. The written consent of the parent or legal guardian of each child will be required for inclusion in the study.

Inclusion/exclusion criteria are in Table 1 below (all inclusion criteria must be met to participate in the study):

**Table 1 Tab1:** Inclusion and exclusion study criteria

Inclusion criteria	Exclusion criteria
Children ≥ 6 months to ≤ 59 months	Children < 6 months and > 59 months
Children ≥ 6 months to ≤ 59 months with Hb > 7 g/dL and no other serious illness	Children ≥ 6 months to ≤ 59 months with Hb ≤ 7 g/dL with signs of other serious illness or Hb < 7 g/dL with signs of clinical decompensation
Sleeps in cluster (i.e. study area) ≥ 90% of nights during any given month	Sleeps in cluster (i.e. study area) < 90% of nights during any given month
Not participating in another clinical trial investigating a vaccine, drug, medical device, or a medical procedure during the trial	Participating or planned participation in another clinical trial investigating a vaccine, drug, medical device, or a medical procedure during the trial
Provision of informed consent form (ICF) signed by the parent(s) or guardian	No provision of ICF signed by the parent(s) or guardian

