After completing the cluster-wide mapping and HH member listing, 45 HHs will be randomly selected from each of the 48 clusters and informed written consent will be obtained to receive SRs. All parents/guardians of these 45 HHs will be approached and read the ICF. Before being asked to sign the ICF, the study enumerators will confirm that the parent/guardian understands the document and that the SR product will be placed in their homes by either study personnel, VHTs, or they need to redeem the SR with a voucher every month. The ICF will also ask that they report to the nearest health facility and/or call the study program manager if they experience any adverse events (AEs) or serious adverse events (SAEs) of interest. AEs and SAEs of interest will be described verbally and will be provided in written form.

Among the 45 selected HHs, a cohort of children will be enrolled to estimate the impact of the SR product on the incidence of malaria disease in the three study arms. In HHs with multiple children that meet the study inclusion criteria, all eligible children will be invited to participate; however, only one will be randomly selected to be enrolled in the study, if eligible. Parents/guardians of children selected to participate in the cohort will be asked to provide consent. An attempt to obtain written, informed consent from both parents of the child will be made, but consent from only one parent will be required for participation (national protocols will be observed).

If parents/guardians of participants consent to enroll in the study, the study team will screen eligible children. After screening children for eligibility, the children will be enrolled. Eligible children will then be tested and treated for malaria free of charge during the study.

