### Methods for additional analyses (e.g. subgroup analyses) {20b}

The per-protocol (PP) population includes the participants from the ITT population who are treated following the specifications of the study protocol without major protocol deviations.

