#### Participants who move to a new house during the intervention follow-up period

For a participant who moves to a different house within the same cluster, that participant will be included in both the ITT and PP analyses. The HH characteristics will be updated at the time the subjects moved.For a participant who moves to a different house in a different cluster, the data from the participant before the participant moves will be included in the ITT analysis. All data from the participant will be included in the PP analysis, both the treatment information and the HH characteristics will be updated at the time the participants moved.

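### Residence is judged by cluster while the spatial repellent hangs only in selected households, so per-protocol follow-up can include time in houses without the product

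*Protocol article*

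**What the plan says.** **Where the product is.** Under Who will take informed consent {26a}, "45 HHs will be randomly selected from each of the 48 clusters and informed written consent will be obtained to receive SRs". Intervention description {11a} places the emanators along interior walls. SR is thus a household intervention within each cluster. The cohort comes from the same households: "Among the 45 selected HHs, a cohort of children will be enrolled".

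**Who counts as resident.** Eligibility criteria {10} works at cluster level. The running text says that children "who report sleeping in selected study clusters > 90% of the nights of each month will be eligible". The inclusion column of Table 1 has "Sleeps in cluster (i.e. study area) ≥ 90% of nights during any given month". The two places differ in the inequality sign. Table 1 also glosses the cluster as the whole study area. Neither place mentions the enrolled household or the structures that hold SR.

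**What happens on a move.** The section on participants who move gives two rules. A participant who "moves to a different house within the same cluster, that participant will be included in both the ITT and PP analyses" has only the household characteristics updated. For a move to a different cluster, all data enter PP and "both the treatment information and the HH characteristics will be updated at the time the participants moved".

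**What PP means.** Methods for additional analyses {20b} limits PP to ITT participants "treated following the specifications of the study protocol without major protocol deviations".

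**The concern.** Exposure is fixed by household, and eligibility by cluster. As written, a child listed in a selected household who usually sleeps in an unselected house of the same cluster qualifies. Because of the study-area gloss, a literal reader could also admit a child who divides nights between clusters of different arms.

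The same test governs retention. Criteria for discontinuing {11b} lets staff end participation when a child no longer meets the inclusion criteria, but a child who moves within the cluster to a house without SR still meets them. Study setting {9} says that population movement is covered by the loss to follow-up rate. These children are not lost: they remain under observation, possibly without product.

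Two readings are at stake. PP should show the contrast among children treated as the protocol specifies. Trial design {8} presents the reference cohort as estimating the direct effect of SR. Both need child-time spent with the product in place. Background and rationale {6a} adds that the evidence is to inform equivalence of impact across delivery systems, so a bias that makes channels look alike, or look different, bears on the message.

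**Working it through.** **1. The two mover rules side by side.**

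| Move | ITT | PP | Updated |
|---|---|---|---|
| Within cluster | kept | kept | household characteristics |
| To another cluster | data before the move | all data | household characteristics and treatment information |

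The within-cluster rule omits the treatment update that its neighbour has. The assigned channel does not change in such a move, but whether the child's house holds SR can. Followed as written, the rule can count time without SR as PP time, which does not fit the PP definition.

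**2. The plan's own precision figure.** Inputs from Sample size {14}: 16 clusters per arm, 40 households per cluster, between-cluster coefficient of variation 0.40, 10% loss, 12 months, 0.5 to 1.0 infections per person-year. The 90% confidence level is in Statistical methods {20a}.

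SE(log HR) = √[(2/16) × (1/e + 0.40²)], with first events per cluster e = 40 × 0.9 × (1 − exp(−rate)); bounds = exp(±1.645 × SE).

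- Rate 0.5: e = 14.2, bounds 0.756 and 1.322.
- Rate 1.0: e = 22.8, bounds 0.769 and 1.300.

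The article gives 0.75 to 0.77 and 1.30 to 1.33, so its figures reproduce to within about 1%. (The wider interval belongs to the lower rate; the article lists them in the opposite order.) These figures do not depend on the residence rule, but the same formula prices the fix in step 5.

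**3. Equal untreated time in both arms.** Assumptions, none given in the article: SR cuts the hazard by E_r in the reference and E_c in a channel, and a share f of child-time is in houses without SR at the full untreated hazard.

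HR = [f_c + (1 − f_c)(1 − E_c)] / [f_r + (1 − f_r)(1 − E_r)]

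With E_r = 30% and E_c = 15%:

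- f = 0: 0.85/0.70 = 1.214.
- f = 10%: 0.865/0.730 = 1.185. Excess hazard hidden: (1.214 − 1.185)/0.214 = about 14%.
- f = 20%: 0.880/0.760 = 1.158. Excess hazard hidden: (1.214 − 1.158)/0.214 = about 26%.

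With E_r = 50% and E_c = 25%, 1.500 becomes 0.775/0.550 = 1.409 at 10% and 0.800/0.600 = 1.333 at 20%.

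**4. Untreated time in one arm only (10%).**

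- 30% v 15%, channel arm only: 0.865/0.70 = 1.236, further from 1.
- 30% v 15%, reference arm only: 0.85/0.73 = 1.164, nearer 1.
- 30% in both arms (true HR 1): 0.73/0.70 = 1.043 or 0.70/0.73 = 0.959.

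**5. Precision cost of censoring untreated time.** Step 2 with the 45 households to be recruited and rate 0.5: e = 45 × 0.9 × 0.393 = 15.9, upper bound 1.316. Multiplying e by 0.9 gives 1.321, and by 0.8 gives 1.328.

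**The case against.** A reader might infer that the rule necessarily pulls the HR toward 1 and so favours a finding of similar channels. The article does not support that. All three arms receive SR, so the pull needs both a true channel difference and similar untreated time in every arm; step 4 shows the other outcomes. Unequal loss is plausible: the household head keeps the voucher, while the other two channels deliver at home visits.

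Other points on that side:

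- **Entry is anchored to households.** Children come from the lists of the selected households and are visited at home every two weeks. At entry only those who habitually sleep elsewhere are affected, and nothing suggests that they are many. This stands, and it limits the size.
- **Sleeping elsewhere is not zero exposure.** Intervention description {11a} claims daytime, early-evening and peri-domestic protection. The full untreated hazard in step 3 is therefore an upper case for children who still spend days at the treated home. This stands too.
- **SR may follow a family that moves.** The article says neither that it does nor that it stops, so a new house cannot be presumed untreated. But the mover rule keeps the child in PP in either case, and that is the defect.
- **PP has covariates for lost exposure.** Travel outside, household application rate and cluster coverage may enter the PP model, and travel is asked at each visit. All are conditional on balance or variation in the data, and none clearly identifies a child sleeping elsewhere in the cluster. Adjustment also leaves the time counted as per protocol.
- **The trial is exploratory and ITT is primary.** Under ITT, keeping children who lose exposure is part of operational effectiveness. This stands, and confines the problem to PP and the direct-effect reading.

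The separate statistical analysis plan is not at hand. The point rests on rules the article states, not on detail it leaves out.

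**Conclusion.** The point holds for the PP analysis and for reading the reference cohort as the direct effect of SR. Cluster-level residence and the within-cluster mover rule allow time in houses without SR to count as per-protocol time, against the article's own PP definition.

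The bias can go either way. Under the assumed 30% and 15% effects, an HR of 1.21 becomes about 1.19 or 1.16 with 10% or 20% untreated time in both arms. With 10% in one arm only it becomes 1.24 or 1.16, and a true HR of 1 becomes 1.04 or 0.96. These figures rest on assumed effects, an assumed untreated share and a full untreated hazard away from SR. The shifts of about 0.02 to 0.06 are small beside stated bounds of roughly 0.75 to 1.33. The effect is likely modest, but the correction is cheap.

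The differing inequality signs are a separate, plain inconsistency. They matter only for a child at exactly 90% and have no bearing on the bias.

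**What to change.** 1. **Eligibility criteria {10}, text and Table 1.** Define residence as usually sleeping in a structure of the enrolled household on the stated share of nights. Use one inequality sign in both places, and delete the gloss that equates the cluster with the study area.
2. **Participants who move to a new house.** At a within-cluster move, record whether the new house has SR. For PP only, count follow-up after the move only while that house has SR under the assigned channel; otherwise censor at the move. Updating exposure at the move, as is done for moves between clusters, is a workable alternative. Leave the ITT rule unchanged.

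**Cost.** One reworded screening question, one recorded item and one PP rule. A few more children may fail screening; Enrollment of the cohort already replaces them with another child or household. The loss of PP precision is negligible (step 5).

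**Timing.** Trial status expected enrolment to finish in August 2024. If it has closed, the PP rule can still be changed before analysis, using whatever the two-weekly visits record about where the child sleeps.

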### Who will take informed consent? {26a}

The study will be explained and consent form read in the local language spoken in the settlement of the following populations:All heads of household (HH) in the selected 48 clusters during the mapping and census activities.Parents or guardians in the 45 HHs randomly selected in each cluster to hang SR in the HH.Parents or guardians of eligible children enrolling into the study in the 45 HHs randomly selected in the 48 clusters.

The study staff will explain the research in the local languages, allow time for answering questions. Once all concerns are addressed, ICFs written in the local language will be signed or a thumb print taken (either on paper or electronically). It will be stressed that entry into the study is voluntary and they may withdraw from the study at any time for any reason without any penalty. If a participant withdraws, their data will remain confidential and used in analysis up until the date of withdrawal. Consented participants will be assigned a participant identity code (or ID card) on enrollment. Consented participants will be screened for inclusion/exclusion criteria.

All individuals from whom written consent is obtained and who cannot sign their names will provide a thumb print on the consent form for documentation to signal their understanding and willingness to participate. A witness not associated with the study will sign the consent form indicating that the ICF was read, and that participation and thumb-printing were given willingly without coercion. Time will be granted to those individuals who would wish to make consultations with their family members before signing.

For participants who cannot read or write, the following procedures will be conducted:The staff member will ensure whenever a participant who cannot read or write is consented, a literate impartial witness (a family or community member of the parent/guardians’ choice) who is not affiliated with the study will be identified and present during the informed consent process.◦ The witness must be present during the entire consent process.◦ The language of ICF used should be the one best understood by both the potential participant or guardian/Legally Authorized Representative (LAR) and the witness.The study staff member will read the ICF, pausing frequently to allow the potential participant, guardian/LAR, or witness to ask questions.The witness will be asked to verify to the best of his/her knowledge that the potential participant understood and agreed with the information provided during the consenting process and all the questions or concerns were addressed satisfactorily.The potential participant or guardian/LAR will be directed by the staff on how to put his/her thumbprint on the appropriate box (both copies). The witness will be verbally instructed to write the name and date for the participant. The witness will then be instructed to write his/her name, sign and date the consent forms in the appropriate spaces provided for the witness.

As part of a cluster-wide mapping of HHs, informed verbal consent will be obtained from all heads of HH in the 48 clusters. All heads of HHs will be approached and read the ICF. The study Data Enumerators will confirm if the head of HHs understands the document and, if eligible, that there is a possibility that they might be selected to receive and hang SR for the duration of the study.

After completing the cluster-wide mapping and HH member listing, 45 HHs will be randomly selected from each of the 48 clusters and informed written consent will be obtained to receive SRs. All parents/guardians of these 45 HHs will be approached and read the ICF. Before being asked to sign the ICF, the study enumerators will confirm that the parent/guardian understands the document and that the SR product will be placed in their homes by either study personnel, VHTs, or they need to redeem the SR with a voucher every month. The ICF will also ask that they report to the nearest health facility and/or call the study program manager if they experience any adverse events (AEs) or serious adverse events (SAEs) of interest. AEs and SAEs of interest will be described verbally and will be provided in written form.

Among the 45 selected HHs, a cohort of children will be enrolled to estimate the impact of the SR product on the incidence of malaria disease in the three study arms. In HHs with multiple children that meet the study inclusion criteria, all eligible children will be invited to participate; however, only one will be randomly selected to be enrolled in the study, if eligible. Parents/guardians of children selected to participate in the cohort will be asked to provide consent. An attempt to obtain written, informed consent from both parents of the child will be made, but consent from only one parent will be required for participation (national protocols will be observed).

If parents/guardians of participants consent to enroll in the study, the study team will screen eligible children. After screening children for eligibility, the children will be enrolled. Eligible children will then be tested and treated for malaria free of charge during the study.

### Additional consent provisions for collection and use of participant data and biological specimens {26b}

Not applicable—there is no anticipated future use of participant blood samples. These samples will be taken only for purposes of RDT diagnosis of malaria infection in the current study.

## Interventions

### Explanation for the choice of comparators {6b}

The study will include separate cohorts to measure the direct effect of SRs as well as the protection to participants using varied distribution channels: paid study personnel (reference arm, positive control), VHTs, and a voucher system.

#### Voucher distribution channel

Trained study staff will confirm how many SR products are needed per structure. The voucher will be a small plastic card with a QR and/or barcode that is programmed with the total number of SR products that will be provided monthly to each head of the HH. The head of HH will retain the voucher.

For the initial month of the study, CRS staff will distribute the voucher and provide the SR during a HH visit along with training on product placement and handling. HH heads will be instructed where (central distribution location) and when (every month) they can redeem the SR product(s). For the remaining 11 months, HH heads will redeem their SRs. Vouchers will be redeemed at central distribution locations in the cluster, chosen by the voucher clusters’ community, for example, a health clinic, or food distribution point. Reminders to redeem their SR will be put in place for this distribution channel.

At the central distribution location, the distributor (trained as part of this study) will scan the voucher QR and/or barcode with an electronic device (e.g., tablet or smartphone). By scanning the voucher, the distributor will know and provide the exact number of SR product(s) to distribute to the HH head. The trained distributor will also request that heads of HHs return their old SR product to the central distribution location (for safe disposal) in exchange for the new ones. If there is a discrepancy in the number of returned SR products versus new ones to be issued, the distributors will still issue the total assigned number of new SRs. They will record reasons for the discrepancy. The CRS study Program Manager will then follow-up on these discrepancies to ensure safe product disposal according to the manufacturer’s instructions. If a HH size changes, the HH head will inform the central distribution location or CRS study personnel, which will kick-off a process by which CRS staff will check the new HH dimensions and re-issue a new QR code on a new voucher corresponding to the updated number of SRs to receive.

